## Part A. Questions Common to All Studies

### A.1. Background and Rationale

A.1.1. Provide a summary of the background and rationale for this study (i.e., why is the study needed?). If a complete background and literature review are in an accompanying grant application or other type of proposal, only provide a brief summary here. If there is no proposal, provide a more extensive background and literature review, including references.

Fragile X syndrome (FXS) is the leading known single-gene cause of autism spectrum disorder (ASD) and the most common inherited form of intellectual disability, resulting in significant functional impairments ([name], [name], & Riley, 2017). The mutation of the FMR1 gene has broad implications for the family. Expansions of the gene occur over generations; therefore, identification of one individual with FXS results in the identification of at least one, and often many, additional family members with an FMR1 mutation. Frequently, multiple children are born into a family before a diagnosis is made (Bailey, [name], Bishop, & Holiday, 2009), which leads to broad family consequences ([name], Bailey, Bann, & Bishop, 2014). Despite documentation that symptoms emerge in the first year of life (Burris, Barry-Anwar, Sims, Hagerman, Tassone, & Rivera, 2017; Roberts et al., 2009; Swanson et al., 2018), the average age of diagnosis is 3 years of age for males with FXS (Bailey et al., 2009). Females with FXS and individuals with the premutation are often diagnosed even later as they typically have a less severe phenotype. The delay of diagnosis can reduce timely access to interventions that could have significant consequences for the developmental trajectories of these children. Furthermore, the delay in diagnosis has significantly limited the ability of researchers to understand the natural progression of symptomology and thereby better address treatment options.

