### A.3. Inclusion/exclusion criteria

A.3.1. List required characteristics of potential subjects (i.e., inclusion and exclusion criteria). If not covered, list also characteristics that would preclude their involvement.

All birthing mothers in North Carolina will be invited to participate in Early Check (IRB #18-0009), a voluntary research program where newborns will be screened for a carefully selected panel of conditions. Early Check is a complement to the state-mandated newborn screening and is conducted in collaboration with the North Carolina State Laboratory of Public Health, utilizing existing newborn blood spots to test for these conditions. It will be offered under a research protocol with parental permission. Children who receive a diagnosis after participation in the Early Check Screening and speak English will be eligible for the intervention and invited to participate.

Self-referrals with infants 12 months of age or younger who have received a diagnosis which was not sought solely due to parental concerns about the infant and who speak English will also be eligible. Infants may not be blind or have a severe hearing impairment as the intervention and assessments are not appropriate for these children. Infants who receive a diagnosis of FXPM after participation in Early Check, speak English, and show signs of delay will be given information about the study and added to the wait-list if interested. FXPM infants who don't show signs of delay but may have increased genetic risk or their parents show anxiety regarding their child's development will also be given information about the study and added to the wait-list if interested. Infants will include both sexes. Families of any race/ethnicity will be invited to participate.

A.3.2. Justify any exclusion based on race, gender or ethnicity

Participants will not be excluded based on race, gender, ethnicity. However, English must be the primary language spoken in the home because all assessment measures and intervention protocol are in English.

A.3.3. Will pregnant women or women who become pregnant be excluded?

No

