## A.8. Data analysis

A.8.1. Summarize the statistical analysis strategy for each specific aim.

For this case series, analyses will be primarily descriptive. Researchers will first examine feasibility and acceptability and descriptive data on pre-post measures at the case level. Next, change scores on each measure over the intervention period will be reviewed to help identify primary outcome measures and effect sizes for a larger trial. Finally, the team will compare developmental and behavior profiles of this sample at age 3 to those of young children with the disorder who were not identified through Early Check (IRB #18-0009).

A.8.2. If this is a pilot study, please describe the future study and say how its study design, aims, sample size, and methods differ from the pilot study you are proposing.

Upon completion of the case series, the team will use data collected on family needs, acceptability and feasibility of the intervention, child skills, parent responsivity, and social validity to refine (1) PIXI and develop a formalized treatment manual for all components, (2) our hypotheses about treatment effects, and (3) our measurement plan. A meeting will be held with consultants and Early Check expert advisors during year 2 of this project to review results and plan next steps. It is anticipated revisions to include manualizing the content and strategies incorporated into parent calls, timing and telehealth revisions, possible adaptations to phase 2 necessary for unique needs of those with rare neurogenetic disorders, and development of fidelity measures for all components.

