First, we are currently working on a collaborative, multisite paper pooling early developmental data collected on young children with FXS. This paper will be based on the Mullen Scales of Early Development (Mullen), administered to over 300 children with FXS under the age of 5 (with an estimated 900+ assessment points) to provide an overview of the extent of delay in five core developmental areas (Cognition, Fine Motor, Gross Motor, Receptive Language, Expressive Language) for boys and girls with FXS under the age of 5. This data will provide a general estimate of functioning at discrete ages to serve as a comparison for those who are identified at birth with FXS and complete the PIXI.

Second, we will publish findings from a soon-to-be-launched survey on parent reports of early development and access to and dosages of early intervention services for a national sample of children under the age of 7 with FX. This will provide additional information about early experiences of young children with FX by which to compare the experiences of our Early Check sample.

And lastly, we will identify, through the RTI Our Fragile X World registry, as well as by working with North Carolina-specific FX advocacy groups (NC CSN and consultant [name]), a sample of children under 5 with FX who have lived in North Carolina for most of their lives ( $n = \sim 15$ ). We will recruit these children and their families into a study about early development of children with FX in North Carolina and will collect direct assessments of these children as well as parent perspectives on their child's access to and dosage of early intervention services in the state. Although this comparison cohort will still be limited by a historical confound, this sample will be our closest possible group to our Early Check (IRB #18-0009) sample.

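### The age-3 comparison likely favours PIXI, by an amount the protocol does not let one compute: the North Carolina comparators have no diagnosis-route rule, and the groups are not PIXI versus no PIXI

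*Protocol*

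**What the plan says.** A.8.1 describes a case series in which "analyses will be primarily descriptive". Its last step compares the sample's profiles at age 3 with those of "young children with the disorder who were not identified through Early Check".

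A.8.3 explains that finding a comparison group for judging efficacy is the difficulty, because too few infants will be identified to power a randomised trial. For the fragile X (FX) sample it names three sources:

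- Pooled Mullen data on over 300 children, "for boys and girls with FXS under the age of 5", intended "to serve as a comparison for those who are identified at birth with FXS and complete the PIXI".
- A national parent survey.
- A North Carolina cohort of about 15, "a sample of children under 5 with FX who have lived in North Carolina for most of their lives", found through a registry and advocacy groups. The protocol calls this its closest available group and admits one limitation, a historical confound.

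A.3.1 admits self-referred infants aged 12 months or younger "who have received a diagnosis which was not sought solely due to parental concerns about the infant". Infants from Early Check are found by newborn screening. B.1.7 lists self-referred infants with FXS, and premutation infants from Early Check, among those who may be invited.

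A.1.1 states that "the average age of diagnosis is 3 years of age for males with FXS", and that females and premutation carriers are often diagnosed later still because they are typically less severely affected.

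**The concern.** The protocol guards the PIXI side against diagnoses driven purely by parental worry and states no such guard for the North Carolina cohort. By its own account of when children are diagnosed, those already known to a registry or advocacy group before age 5 would tend to be the more visibly affected and more often boys. PIXI infants could then look better at age 3 with no intervention effect. This is a different problem from calendar time, which is all that a historical confound covers.

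The groups are also not cleanly PIXI versus no PIXI, and one sentence in A.8.3 conditions the PIXI side on completion. This is the study's only between-group evidence on PIXI, so a slanted contrast would affect what readers conclude and could carry into the effect size expected in the next trial.

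**Working it through.** **1. The two sides as the protocol defines them**

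| Feature | PIXI infants | North Carolina cohort |
|---|---|---|
| Route to diagnosis | Screening; or self-referral with a diagnosis not sought only because of parental concern (A.3.1) | No criterion stated (A.8.3) |
| Age condition | Self-referrals 12 months or younger | Under 5; none on age at diagnosis |
| Mutation status | May include premutation infants (A.3.1, B.1.7) | FX, not further specified |
| Sex | Both, no ratio given (A.3.1) | Nothing stated |

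**2. The group label.** A self-referred PIXI infant was not identified through Early Check. That infant belongs to the PIXI sample and also meets the A.8.1 description of a comparator. The label splits by screening programme, not by receipt of PIXI.

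**3. Completion.** The Mullen sentence in A.8.3 takes only those identified at birth who finish PIXI. A.7.3 says families who cancel often may be given an end date and not complete. Completion is therefore selective, and self-referrals drop out of that contrast altogether.

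**4. Size.** There is no figure to reproduce: A.8.3 gives no alpha, power, effect size or SD. The documents also give no sex ratio, sex gap or severity distribution. Every input below is an assumption, the PIXI effect is set to zero, and results are in SD units in favour of PIXI.

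*Sex mix.* Bias = (female share in PIXI − female share in comparators) × sex gap.

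- 50% v 50%: 0 at any gap.
- 50% v 35%, gap 0.5 SD: 0.15 × 0.5 = 0.08.
- 50% v 20%, gap 1.0 SD: 0.30 × 1.0 = 0.30.
- 50% v 10%, gap 1.5 SD: 0.40 × 1.5 = 0.60.

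*Severity-led diagnosis.* Bias = ρ × φ(z)/f, a normal selection model. Here f is the fraction of affected children already diagnosed, z the matching cut-point, φ the normal density, and ρ the correlation of early diagnosis with severity. PIXI infants are taken as unselected on severity.

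| f | ρ = 0 | ρ = 0.2 | ρ = 0.4 | ρ = 0.6 |
|---|---|---|---|---|
| 0.9 | 0 | 0.04 | 0.08 | 0.12 |
| 0.7 | 0 | 0.10 | 0.20 | 0.30 |
| 0.5 | 0 | 0.16 | 0.32 | 0.48 |
| 0.3 | 0 | 0.23 | 0.46 | 0.70 |

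The two terms overlap, because sex is one reason for later diagnosis, so they should not simply be added.

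**5. Against sampling error.** With 15 comparators and m PIXI children (m assumed), the 95% half-width is 1.96 × √(1/15 + 1/m). The difference detectable at 80% power (two-sided 5%) is (1.96 + 0.84) × √(1/15 + 1/m).

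| m | Half-width (SD) | Detectable (SD) |
|---|---|---|
| 15 | 0.72 | 1.02 |
| 30 | 0.62 | 0.89 |
| 45 | 0.58 | 0.84 |

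If a test were run, a pure bias of 0.3 SD would give a nominal 5% difference 13% to 17% of the time across these sizes, and 0.5 SD would give one 28% to 39% of the time. Equal sex mix and the same diagnosis-route rule on both sides (ρ = 0) bring both bias terms to zero in this model.

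**The case against.** The strongest reply is that this is a descriptive case series. The age-3 contrast comes last, no test is attached to it, A.8.2 expects a randomised wait-list trial next, and A.8.3 treats the Mullen data as a general estimate. That stands: no error rate is at risk. It does not dispose of the point, because A.8.3 offers these groups as the answer to the missing randomised comparison.

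Four stronger readings are tempting, and the documents do not support them:

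- *That sex is ignored.* The Mullen overview is described for boys and girls and may be reported by sex, and stratification could sit in an analysis plan not shown. What can be said is that nothing is stated for the North Carolina cohort.
- *That all comparators were diagnosed on symptoms.* The protocol does not say so. A.1.1 notes that one diagnosis often leads to others in the family, so some may have been found through a relative. The cohort is also under 5, not diagnosed by 3, which weakens the selection. On the other side, the A.3.1 rule excludes only diagnoses sought *solely* through parental concern, so partly symptom-led diagnoses can enter PIXI.
- *That the whole analysis is confined to completers.* The completion wording appears only in the Mullen sentence; A.8.1 refers to the sample.
- *That the bias has a known size.* It does not.

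A practical objection also stands. Using only family-history diagnoses as the main comparator set could leave very few of about 15 children, and intake questions cannot reach pooled Mullen data already collected.

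**Conclusion.** The comparison as written is likely biased in favour of PIXI, and the documents do not allow the amount to be computed. The direction is an inference from the A.1.1 account of who is diagnosed when. It assumes that the North Carolina children were largely diagnosed outside screening and that no other selection offsets it.

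The ranges above, from zero to 0.60 SD for sex mix and to 0.70 SD for severity-led diagnosis, show only that a bias of the same order as the sampling uncertainty is possible. A single value read from them, such as 0.30 SD (4.5 points on a scale with SD 15), is purely illustrative.

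Three points need no assumption: the North Carolina cohort has no diagnosis-route criterion, only a historical confound is acknowledged, and the A.8.1 label does not separate self-referred PIXI infants from comparators. The harm is to interpretation of the age-3 contrast, not to the feasibility and acceptability aims. It should be corrected soon, because A.8.3 says the comparison activities are under way and a reason for diagnosis not collected at intake may not be recoverable.

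**What to change.** In A.8.1 and A.8.3:

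1. Define the contrast as PIXI versus no PIXI. Against the FX comparators, use full-mutation FXS infants and show premutation infants separately. This limits only the FX contrast; infants with other disorders stay in the descriptive analyses.
2. Include every enrolled infant with an age-3 assessment, whether or not sessions were completed, and show Early Check and self-referred infants separately.
3. Record reason for diagnosis and age at diagnosis in the North Carolina cohort at intake. Report results by diagnosis route as a sensitivity display, without making family-history diagnoses the sole main set. B.1.5 already asks self-referred families for the age at diagnosis.
4. Report the comparison by sex, using sex-specific values from the pooled Mullen data where available.
5. Name ascertainment bias and its likely direction beside the historical confound.

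The cost is two intake questions and some re-labelled tables. The downside is small descriptive subgroups within about 15 comparators, with wide intervals and the risk of identifying individuals that A.10.6 already notes. The route display cannot be extended to the pooled Mullen data unless route was recorded there.

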#### A.8.4. Summarize the plans for data management.

Assessment data will be entered and managed via REDcap by RTI research team members. Physical assessment protocols will be deidentified and securely stored at RTI. Video and audio files will be stored on a secure server at UNC or RTI.

The security standards for the protection and integrity of all data are described in Section A.10 and include storage on a HIPAA-compliant server in the RTI Enhanced Security Network, two-factor authentication, and back-up of the data performed by RTI ITS daily. Data access will be limited only to those team members who require access to perform data entry and analysis.

Regular review and data checks will be performed throughout all data collection and analysis activities in order to prevent, identify and correct any errors. All data analysis activities will be performed independently by two team members and compared for accuracy. The Principal Investigator is responsible for the final review of all analyses.

## A.9. Identifiers

### A.9.1. Check which of the following identifiers you already have or will be receiving, or select "None of the above."

- ☒ Names (this would include names/signatures on consent forms)
- ☒ Telephone numbers
- ☒ Any elements of dates (other than year) for dates directly related to an individual, including birth date, admission date, discharge date, date of death. For ages over 89: all elements of dates (including year) indicative of such age, except that such ages and elements may be aggregated into a single category of age 90 and older
- ☒ Any geographic subdivisions smaller than a State, including street address, city, county, precinct, zip code and their equivalent geocodes (e.g. GPS coordinates), except for the initial three digits of a zip code
- ☐ Fax numbers
- ☒ Electronic mail addresses
- ☐ Social Security numbers
- ☐ Medical record numbers
- ☐ Health plan beneficiary numbers
- ☐ Account numbers
- ☐ Certificate/license numbers
- ☐ Vehicle identifiers and serial numbers (VIN), including license plate numbers
- ☐ Device identifiers and serial numbers (e.g., implanted medical device)
- ☐ Web universal resource locators (URLs)
- ☐ Internet protocol (IP) address numbers
- ☐ Biometric identifiers, including finger and voice prints
- ☒ Full face photographic images and any comparable images

✗ Any other unique identifying number, code, or characteristic, other than dummy identifiers that are not derived from actual identifiers and for which the re-identification key is maintained by the health care provider and not disclosed to the researcher

✗ None of the above

A.9.2. For any identifiers checked, how will these identifiers be stored in relationship to the research data?

✗ with the research data (i.e., in the same data set and/or physical location)

✓ separate from the research data (i.e., coded with a linkage file stored in a different physical location)

**Provide details** about the option you selected above:

Identifiers will be stored separately from research data in a password protected document linking identifying information to a participant's ID number.

A.9.3. Are you collecting Social Security Numbers to be used as a unique identifier for study tracking purposes for national registry or database? (Do not check yes if collecting SSN *only* for payment purposes; this will be addressed later.)

No

## A.10. Confidentiality of the data

A.10.1. Describe procedures for maintaining confidentiality of the data you will collect or will receive (e.g., coding, anonymous responses, use of pseudonyms, etc.).

Only personnel who have completed the required human ethics trainings will have access to individuals private, identifiable information. All participants will receive a unique identification number (ID) that will be used for any documents, videos, and materials related to the child. Names associated with the ID will be kept in password-protected document on a secure computer server. All family/child paper and/or electronic data will be stored in a locked cabinet or in an encrypted computer and identified only by child ID. All video recorders will be stored in a locked cabinet. Videos will be removed and deleted from cameras and stored on a secure serve in a timely manner. Any scientific reports, article submissions, or summaries of data will not include children/family names. Data will be presented in a summary format that will prevent any personal identification.

A.10.2. Describe how data will be transmitted among research team (i.e., personnel listed on this application).

Questionnaire data will include only ID numbers and be entered directly into secure REDCap database systems. Any hard copy data will be transported directly to a UNC or RTI office in a confidential portable file in a locked file box and entered in the office for access by the team. De-identified data only will be transmitted within the research team by password protected, encrypted email. Access to the data files will be restricted, based on the role of the research team member.

A.10.3. Are you collecting sensitive information such as sexual behavior, HIV status, recreational drug use, illegal behaviors, child/physical abuse, immigration status, etc?

No

A.10.4. Do you plan to obtain a federal Certificate of Confidentiality for this study? Please note that all ongoing or new research funded by NIH as of December 13, 2016 that is collecting or using identifiable information is [automatically issued a Certificate of Confidentiality](#) (CoC). You should also select "Yes" if your study is NIH funded and has been issued a CoC under this updated NIH policy.

NOTE: Investigators utilizing ANY federal funding to conduct this research should review the [COC website](#) to determine if their funding agency issues COCs automatically (as the NIH does) or if they might need to apply for the COC via the online COC system. Unfunded and non-federally funded investigators may also apply for a COC via [the online COC system](#).

No

A.10.5. If this study is limited to data collection by survey or interview, discuss the potential for deductive disclosure (i.e., directly identifying subjects from a combination of indirect IDs).

The primary potential for deductive disclosure will be through videotaping of research participants. Videotapes

of intervention sessions will be viewed and coded for parent responsivity. Videotapes will have full face images of children and family and it is likely first names will be used throughout the interaction with interventionist, creating a potential for identification. We, therefore, will take careful measures to protect the security of videotapes. The IDs used for other assessments and materials offer little potential for deductive disclosure.

A.10.6. Will any of the groupings or subgroupings used in analysis be small enough to allow individuals to be identified?

Yes

Describe these groupings and sample sizes projected.

There is a possibility that participating individuals could be identified based on knowledge of infants who have a confirmed positive diagnosis of a rare disorder. Even with the most liberal of estimates of uptake for the Early Check program (IRB #18-0009), we would still only anticipate identifying around 10-20 infants per year.

